#### 2.3.1. Primary Outcome

In the surgical group, we will assess mean glycaemia as a continuous outcome variable, glycaemic variability (standard deviation) as a continuous outcome variable, and birth weight as a continuous explanatory variable. Linear mixed models will be used for the primary outcome analysis. The outcome variables will be measured at four time points for each subject. Confounders will be added to the model as covariates.

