-Maternal glycaemic outcomes: percentage of time < 54 mg/dL (ADA recommendations of the definition of hypoglycaemia) [24]; glycaemic variability metrics: standard deviation (SD), Coefficient of Variation (CV) and Mean Amplitude of Glucose Excursions (MAGE); percentage of time > 120 mg/dL; percentage of time > 140 mg/dL; percentage of time > 180 mg/dL; percentage of time < 70 mg/dL; percentage of time < 63 mg/dL; percentage of time < 50 mg/dL; low blood glucose index (LBGI)-Maternal pregnancy outcomes: duration of pregnancy; time from surgery to conception; prevalence of micro- and macronutrient deficiencies; body composition in early pregnancy as assessed by bio-impedance measurement, prevalence of GDM; gestational weight gain (GWG); prevalence of caesarean section; prevalence of pre-eclampsia and eclampsia, prevalence of gestational hypertension; surgery-related complications during pregnancy; type of labour; type of delivery; complications during delivery-Foetal growth and body composition outcomes: prevalence of SGA; large for gestational age (LGA); prevalence of intra-uterine growth retardation (IUGR); FASTT; pregnancy loss-Neonatal outcomes: body composition of the newborn assessed by skin fold thickness measurements, according to [25]; prevalence of preterm delivery; prevalence of neonatal hypoglycaemia; prevalence of neonatal intensive care unit (NICU) admission; foetal malformation; complications during delivery; sex of the infant; birth weight, length, and percentile; neonatal death-Identification of new biomarkers: metabolomics on maternal plasma collected at 30–34 weeks: lipid omics platform and metabolism and energy platform. We will prioritise analyses for the surgical group.-Patient-reported outcomes: certain potential confounders, such as smoking status, will be derived from survey data. Additionally, other patient-reported outcomes collected through the surveys will be analysed as independent outcomes in the exploratory comparisons between subgroups. The following questionnaires will be completed at the different study visits:A self-designed questionnaire on general habits and socio-economic background previously used in the Belgian Diabetes in Pregnancy study (BEDIP) to extensively collect information on socio-economic status and habits [22].A self-designed questionnaire on the user-friendliness of the masked CGM, based on the CGM Satisfaction Scale (CGM-SAT) [26], the Glucose Monitoring Experiences Questionnaire (GME-Q) [27], and the Glucose Monitoring Satisfaction Survey (GMSS) [28].Frequency Food questionnaire (FFQ), including questions on frequency and portion size of consumed foods and beverages validated for the Belgian population [29].International Physical Activity Questionnaire (IPAQ, full version) validated for use in the Belgian population and as used in the BEDIP study [22]. This questionnaire assesses various domains of physical activity, including job-related tasks, caregiving, and time spent sitting.The 36-Item Short Form Health Survey (SF-36) includes a set of generic, coherent, and easily administered quality of life measures and is validated for use in the maternity context [30].The 20-item Centre for Epidemiologic Studies-Depression (CES-D) questionnaire, which is validated in pregnancy to asses symptoms of clinical depression over the past seven days [31].The State-Trait Anxiety Inventory (STAI) questionnaire, a validated six-item short-form on anxiety, which is validated for the Dutch speaking population [32].

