#### 2.9.1. Sample Size and Power Calculation

The sample size (n = 95) was calculated based on the best available data on CGM in pregnancy with MBS [40,41]. The study provides 80% power to detect a moderate association (effect size = 0.3) between glycaemia measures (mean and variability) and birth weight at a significance level of *p* < 0.05. Repeated CGM measurements (four one-week periods per participant) were accounted for using a cluster size of four and assuming an interclass correlation (ICC) of 0.5. A drop-out rate of 30% was assumed, in the sense that 30% of all measurements would be missing. The sample size was decided considering adjustment for four variables in the analysis. A Bonferroni correction will be applied to control for multiple comparisons, resulting in a 2.5% test-wise significance level.

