#### 2.9.2. Statistical Methods

##### Primary and Secondary Analyses (MBS Group)

The primary analysis will be performed using linear mixed models, adjusted for confounders. Mean glycemia refers to the mean interstitial glucose level measured via CGM throughout pregnancy. Glycaemic variability reflects fluctuations in blood glucose levels and is quantified using variables such as SD, CV, and MAGE derived from CGM. Repeated measurements will be used for the primary outcome analysis, with mean glycemia and glycaemic variability treated as continuous outcome variables, and birth weight as the explanatory variable. To account for clustering due to repeated measures, linear mixed models will be used with a random intercept for the subject. Confounders such as smoking, hypertension, nutrient deficiencies, insufficient gestational weight gain, and time from surgery will be added to the model as covariates to determine the independent association between birth weight and glycaemic parameters. Variables will be considered confounders if they are associated with both birth weight and glycaemic parameters. Linear slopes with 95% confidence intervals will describe the association between glycaemic parameters and birth weight. No specific action is taken to deal with missing CGM results given the fact that the analysis model is likelihood-based and known to provide unbiased results under the fairly general assumption of missingness at random [42]. Statistical analysis will be performed by SAS version 9.4; all tests will be two-sided with significance set at *p* < 0.05.

Secondary outcomes, including time spent <54 mg/dL and hyperglycaemic thresholds (>120 mg/dL and >140 mg/dL), will be analysed analogously.

Third, associations between glycaemic patterns and binary neonatal outcomes, including SGA and birth defects, will be assessed similarly using linear models for repeated measurements. Mean differences with 95% confidence intervals will be estimated between cases with and without the specified adverse outcome.

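### The analysis section puts every test at 5%, while the sample-size section sets 2.5% for each primary test, so the threshold for the primary result is not unambiguous

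*Protocol article*

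**What the plan says.** **Significance level.** Section 2.9.1 (Sample Size and Power Calculation) states: "The study provides 80% power to detect a moderate association (effect size = 0.3"), and continues "between glycaemia measures (mean and variability) and birth weight at a significance level of" p < 0.05. The same paragraph ends: "A Bonferroni correction will be applied to control for multiple comparisons, resulting in a 2.5% test-wise significance level".

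Section 2.9.2, under Primary and Secondary Analyses (MBS Group), opens with the primary analysis and closes by saying that "all tests will be two-sided with significance set at" p < 0.05. On estimation it says: "Linear slopes with 95% confidence intervals will describe the association between glycaemic parameters and birth weight". It mentions neither the Bonferroni correction nor a different level for the primary tests.

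**Variability measure.** Section 2.3.1 (Primary Outcome) specifies "glycaemic variability (standard deviation) as a continuous outcome variable", beside mean glycaemia. Section 2.9.2 says that variability "is quantified using variables such as SD, CV, and MAGE derived from CGM", and its next sentence makes glycaemic variability an outcome of the primary analysis. Section 2.3.3 (Exploratory Outcomes) lists "glycaemic variability metrics: standard deviation (SD), Coefficient of Variation (CV) and Mean Amplitude of Glucose Excursions (MAGE").

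**The concern.** The two levels cannot both govern the same tests. Suppose the slope for mean glucose has p = 0.03. Under 2.9.1 it is not significant. Under 2.9.2 it is, and its 95% interval excludes zero. The conflict thus decides whether the primary result is declared positive.

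Multiplicity matters here because section 2.3 frames the aim as showing an association of birth weight with mean glycaemia *or* with variability, so either test can carry the claim. That is the situation the Bonferroni split is meant for.

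The open list of metrics adds a smaller ambiguity of the same kind. A 2.5% level is exact Bonferroni for two tests. It no longer holds the overall error at 5% if the coefficient of variation or MAGE can join, or replace, the standard deviation as a primary measure after the data are seen.

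**Working it through.** **1. Which level produced n = 95?**

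Inputs, all from section 2.9.1: effect size 0.3, 80% power, four adjustment variables, four measurements per woman, intraclass correlation 0.5, 30% of measurements missing. The article does not name the scale of the effect size; I read it as a correlation.

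- Independent observations: n = ((z(1−α/2) + z(0.80)) / atanh(0.3))² + 3 + 4, with atanh(0.3) = 0.3095 and z(0.80) = 0.8416.
- Design effect: 1 + (4 − 1) × 0.5 = 2.5.
- Women: n × 2.5 / 4 / 0.7.

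| Two-sided α | z(1−α/2) | Independent observations | After clustering | After 30% missing |
|---|---|---|---|---|
| 0.025 | 2.2414 | 106.22 | 66.38 | 94.83, i.e. 95 |
| 0.05 | 1.9600 | 88.93 | 55.58 | 79.40, i.e. 80 |

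The stated 95 is reproduced at 2.5% and not at 5%. Other conventions shift the figure:

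- Rounding 106.22 up to 107 before the later steps gives 96.
- Using the expected cluster size of 2.8 gives about 73 at 2.5% and 61 at 5%.
- Using 2.8 and also dividing by 0.7 gives 103 at 2.5% and 87 at 5%.

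None of the clustered variants tried at 5% reaches 95.

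**2. Power of 95 women.** Effective n = 95 × 4 × 0.7 / 2.5 = 106.4. Power = Φ(0.3095 × √(106.4 − 7) − z(1−α/2)).

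- α = 0.025: Φ(3.086 − 2.241) = 80.1%.
- α = 0.05: Φ(3.086 − 1.960) = 87.0%.

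The stated 80% is the power at the 2.5% test-wise level.

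**3. Family-wise error for the two primary tests.** The upper bound is m × α; under independence the error is 1 − (1 − α)^m.

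- Two tests at 2.5% (2.9.1 with 2.3.1): bound 5%; independent 1 − 0.975² = 4.94%.
- Two tests at 5% (2.9.2 as written): bound 10%; independent 1 − 0.95² = 9.75%.

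**4. The variability measure.** 0.05 / 0.025 = 2 tests, which matches mean glucose plus one variability measure. Section 2.3.1 names that measure as the standard deviation, and 2.3.3 places the coefficient of variation and MAGE among the exploratory outcomes. Only 2.9.2 leaves the choice open.

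**The case against.** The strongest reply is that the article does commit to error control. Section 2.9.1 says the correction will be applied, the sample size bears this out, and 2.3.1 gives exactly two primary outcomes. Read together, these hold family-wise error at 5% or below. This stands, and it rules out three stronger readings that a reader might infer:

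- *Family-wise error is not controlled.* The documents support only that it is not unambiguously controlled. Control is lost if 2.9.2 is followed in place of 2.9.1.
- *There are four primary tests.* Four tests at 5% would give 18.5% if independent, and four at 2.5% would give 9.6%. But the sentence in 2.9.2 is a general description in a subsection that also covers secondary analyses, while 2.3.1, 2.3.3 and the 2.5% level all point to the standard deviation alone. Independence is also implausible for three metrics from the same glucose traces. These are worst cases, not the size of the problem.
- *The power statement in 2.9.1 is wrong.* Its 5% reads naturally as the overall level, which the Bonferroni sentence then divides. It lacks a label; it is not an error.

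It can also be said that 95% intervals merely describe the slopes and need not match the test level. That is fair: such intervals are not an error in themselves, though here they would exclude zero for some results that fail the 2.5% test.

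What the reply does not answer is the word *all* in 2.9.2, in the section that specifies the primary analysis. Nor is this a detail left to an unseen analysis plan: the article states two incompatible rules, and a later plan would have to overrule one of them.

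**Conclusion.** The point holds as a conflict over the decision threshold. Section 2.9.1 tests each primary association at 2.5%; 2.9.2 tests everything at 5%. Any primary p-value between 0.025 and 0.05 is classified differently by the two sections. If 2.9.2 is followed, family-wise error for the two primary tests rises from at most 5% to at most 10% (9.75% if independent). The open list of metrics in 2.9.2 is a secondary ambiguity, which the rest of the article resolves in favour of the standard deviation.

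The inference that 2.5% was intended rests on reading 0.3 as a correlation and on applying the design effect for the full cluster of four before allowing for missing measurements. The conflict itself and the error bounds depend on neither assumption. The sample size is sound for the 2.5% level on that reading. The wording should be settled before the data are analysed, because it determines whether the primary result counts as positive.

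**What to change.** In 2.9.2, replace the blanket significance statement with:

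> The two primary tests (mean glucose; SD) are each carried out two-sided at 2.5%, and 97.5% confidence intervals are given for these slopes, alone or beside the 95% intervals. Other tests use a two-sided 5% level unless a correction is stated elsewhere (metabolomics: Bonferroni) and are not confirmatory.

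The exception is needed because section 2.8.11 already applies Bonferroni to the metabolomics tests.

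Also in 2.9.2, name the standard deviation as the only primary variability measure, as 2.3.1 does, and keep the coefficient of variation and MAGE exploratory, as in 2.3.3.

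In 2.9.1, label p < 0.05 as the overall level and state that the 80% power applies at the 2.5% test-wise level.

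The cost is wording only. The sample size of 95 is unchanged. Primary significance becomes slightly harder to reach than under 2.9.2 as written, which the sample size already assumes.

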##### Exploratory Comparative Analyses

The control group will be manually matched in a 1:1 ratio based on age and pre-pregnancy BMI before participation. A comparison of both groups on participant characteristics such as parity, insufficient GWG, hypertension, micronutrient deficiencies, and smoking status will be performed using Fisher exact tests. The comparison between the MBS and control group on birth weight and glycaemic measures will be performed using linear mixed models with a random intercept to account for clustering by matching. Confounders will be included as covariates in the model in case they were shown to differ between groups. Group comparisons on binary variables such as adverse pregnancy outcomes will be performed using a similar approach, applying generalised linear mixed models for binary responses.

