
## 1. Background

Obesity is associated with increased risks for miscarriages, gestational diabetes mellitus (GDM), preeclampsia, and caesarean delivery [1]. Metabolic and bariatric surgery (MBS) is the most effective treatment for obesity and its related comorbidities [2]. Of all patients who undergo MBS, up to 80% are women of childbearing age [3]. As such, pregnancies in women with a history of MBS are becoming increasingly prevalent. Surgically induced metabolic changes benefit mother and child but can also lead to adverse pregnancy outcomes. Several nationwide register-based cohort studies and systematic reviews have shown that MBS is associated with lower risks for macrosomia, GDM, and hypertensive disorders, but with increased rates of small-for-gestational-age (SGA) infants, preterm delivery, and perinatal mortality [4,5,6,7,8]. Children born SGA are at an increased risk of developing type 2 diabetes and cardiovascular diseases in the long-term [9]. The fact that the increased risks of SGA and preterm deliveries remain when matching for pre-pregnancy weight suggests that MBS as such is associated with adverse obstetric outcomes, and not only through weight reduction [7]. A continuous decline in foetal growth throughout pregnancy has been demonstrated after Roux-en-Y gastric bypass (RYGB), starting at the beginning of the second trimester [10]. In addition, the foetal abdominal subcutaneous tissue thickness (FASTT) was markedly decreased in foetuses of mothers with a history of MBS [11].

The underlying mechanisms of foetal growth restriction in this population remain unclear but are likely multifactorial. Potential contributors include nutrient deficiencies, placental dysfunction, altered glucose metabolism, and potentially changes in other metabolic pathways. A prospective cohort study including 54 women with previous MBS confirmed reduced foetal growth in pregnancies following surgery and evaluated fetoplacental Dopplers as a proxy for placental function [12]. However, no alterations in fetoplacental circulation or correlations with foetal size were observed [12].

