#### 2.3.3. Exploratory Outcomes

An overview of clinical definitions and diagnostic criteria considered in this study is given in a supplemental table, Table S1. The self-designed questionnaire on the user-friendliness of the masked CGM for both groups is given in Tables S2 and S3. These outcomes will be analysed for both the surgical and the control group.

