#### 2.8.4. Biochemical Parameters and GDM Screening

Lab measurements will be performed in line with normal routine. Based on recommendations for micronutrient monitoring during pregnancy after MBS, vitamin A (µg/L), 25-OH-Vitamin D (µg/L), vitamin B12 (ng/L), folate (µg/L), prothrombin time (s, %, INR), iron (µg/dL), transferrin saturation (%), and ferritin (µg/L) will be measured every trimester in the surgical group [34]. Micronutrient monitoring in the control group will be conducted based on clinical judgement.

At first prenatal visit, screening for overt diabetes will be performed using fasting plasma glucose (FPG, mg/dL), or HbA1c (%) if fasting is not feasible. Women with a history of bariatric surgery will undergo screening for GDM at 24–28 weeks of pregnancy and will perform SMBG for a maximum of one week, as previously described [34]. At 24–28 weeks, the control group will be screened using a 50 g glucose challenge test. However, women with a history of GDM, obesity, or impaired fasting glycaemia in early pregnancy will undergo a 75 g OGTT, according to the 2019 Flemish guidelines [35]. An overview of diagnostic criteria for GDM in both groups is provided in Supplemental Table S1.

Specifically for this study and for all participants, at each study visit (6–12 weeks, 18–22 weeks, 24–28 weeks, and 30–34 weeks) and at delivery when cord blood is collected, two additional plasma samples will be collected for long-term storage at the biobank of UZ Leuven to allow for future analysis of metabolomics.

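### In the exploratory matched comparison, micronutrient deficiency is tested between groups and can become a covariate although it is ascertained unequally, and the covariate rule admits variables that arise after surgery and conception

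*Protocol article*

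**What the plan says.** **Measurement of micronutrients.** Section 2.8.4 says that the panel "will be measured every trimester in the surgical group". For the other group it says: "Micronutrient monitoring in the control group will be conducted based on clinical judgement". Section 2.8.2 also ties the trimester panel to the surgical group. Table 1 lists the micronutrient lab at three visits (before 12, 18–22 and 30–34 weeks) without limiting it to a group, although other rows of that table do name one.

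**Use of micronutrients in the group comparison.** Section 2.9.2, under Exploratory Comparative Analyses, states that the comparison on parity, "insufficient GWG, hypertension, micronutrient deficiencies, and smoking status will be performed using Fisher exact tests". It then sets the covariate rule: "Confounders will be included as covariates in the model in case they were shown to differ between groups". The models concern birth weight and glycaemic measures, with a random intercept for matching, and binary outcomes are handled in a similar way.

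**GDM.** Under Section 2.8.4 the surgical group "will perform SMBG for a maximum of one week, as previously described", whereas "the control group will be screened using a 50 g glucose challenge test", or with a 75 g OGTT if certain risk factors are present. Section 2.3.3 lists the prevalences of deficiency and of GDM among the exploratory outcomes and says: "These outcomes will be analysed for both the surgical and the control group".

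**Background.** Section 1 reports that "MBS is associated with lower risks for macrosomia, GDM, and hypertensive disorders" and counts nutrient deficiency among the possible contributors to restricted foetal growth.

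**The concern.** Three things follow from these passages.

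1. A between-group test of deficiency compares scheduled testing with testing at a clinician's discretion. A difference can appear when true prevalence is equal. The covariate rule then carries that difference into the birth-weight and glycaemia models. A later analysis plan can say how untested women are coded, but it cannot recover values that were never measured.

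2. The rule picks covariates by an observed difference, and the only screen described is a set of significance tests. It can admit variables that arise after surgery and conception. The article itself places deficiency on a possible pathway to poor growth and links surgery to fewer hypertensive disorders. If the target is the total difference between women with and without surgery, adjusting for such variables can take away part of it.

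3. A difference in GDM prevalence mixes disease frequency with the test used to find it.

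At stake are the exploratory statements about how pregnancies after surgery differ from matched pregnancies without it.

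**Working it through.** **The plan's own figure.** The group size of 95 reproduces if the effect size of 0.3 is read as a correlation (an assumption). With two-sided alpha 0.025, 80% power and four covariates:
- ((2.2414 + 0.8416)/0.3095)² + 3 + 4 = 106.22
- times (1 + 3 × 0.5)/4 = 66.38
- divided by (1 − 0.30) = 94.83, so 95.

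This point does not dispute that number. With 1:1 matching, the comparison below uses 95 v 95.

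**Step 1: can unequal testing alone produce a difference?** The article gives no prevalence and no control testing rate, so both are assumed. Let true prevalence p be equal in the two groups, let all deficiencies be found after surgery, let a share s be found in controls, and let a deficiency that is not found count as absent. Observed proportions are then p and p × s. The table gives the exact probability that a two-sided Fisher test at 0.05 rejects.

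| p | s = 100% | s = 75% | s = 50% | s = 25% |
|---|---|---|---|---|
| 20% | 0.034 | 0.11 | 0.42 | 0.86 |
| 30% | 0.035 | 0.17 | 0.65 | 0.98 |
| 50% | 0.035 | 0.35 | 0.93 | 1.00 |

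At p = 30% and s = 50%, for example, the expected counts are 0.30 × 95 = 28.5 and 0.15 × 95 = 14.25, with no true difference. If untested women are instead treated as missing, they drop out of any model that contains deficiency, and the tested controls who remain are a selected group.

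**Step 2: what does the covariate rule then do to birth weight?** This is a simulation of 95 matched pairs with 4,000 runs. The assumptions are a direct group effect of −100 g, a deficiency effect of −200 g, SD 450 g and within-pair correlation 0.1. Deficiency enters only if Fisher p < 0.05. Regression on pair differences stands in for the mixed model. Total effect = −100 − 200 × (prevalence after surgery − prevalence in controls).

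| True prevalence, surgery v control | Share found in controls | True total | Unadjusted | Rule in the plan | Covariate enters |
|---|---|---|---|---|---|
| 30% v 30% | 100% | −100 g | −100 g | −100 g | 3% |
| 30% v 30% | 50% | −100 g | −101 g | −79 g | 65% |
| 50% v 25% | 100% | −150 g | −150 g | −103 g | 93% |
| 50% v 25% | 50% | −150 g | −150 g | −78 g | 100% |

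The third row is adjustment for a pathway variable: the result is close to the direct effect, not the total. In the fourth row the result falls short of both the total (−150 g) and the direct effect (−100 g). Across the last three rows the shift from the true total is about 20 to 70 g towards zero. In the first row there is none.

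**Step 3: GDM.** Assume true prevalence of 15% in both groups. If one group's test finds 70% or 50% of what the other's finds, the observed gap is 0.15 × 0.30 = 4.5 points or 0.15 × 0.50 = 7.5 points. The test rejects with probability 0.11 or 0.29.

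**The case against.** The best defence is that the comparison is labelled exploratory and that the size of any distortion rests on figures the article does not give. Both are true. If clinicians test the controls they suspect, a large share of control deficiencies may be found. At an assumed 40% prevalence with three quarters found, about 38 v 28 or 29 cases would be expected (Fisher p about 0.17 to 0.22), so no significant gap is expected there. How untested women are coded is also a detail that may sit in an analysis plan that is not shown. What remains is that the article itself schedules unequal measurement and then tests the result between groups.

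A reader might go further in four ways that the article does not support:
- **That the matched comparison is biased.** It can be. This depends on the estimand, which is not stated, on the share of control deficiencies found, and on whether the covariate enters. A model net of weight gain could be a legitimate secondary question.
- **That GDM screening distorts the covariate choice.** GDM is not named in the screen. The list is open, so GDM is not ruled out, but the demonstrated problem with GDM is as an outcome.
- **That every screened variable is an effect of surgery.** Parity and smoking are ordinary confounder candidates. Section 1 supports the link to surgery for hypertensive disorders but not for gestational weight gain, which is simply measured after conception.
- **That missing control values would break the matched pairs.** A mixed model with a random intercept does not need complete pairs. The loss would be of the untested women.

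Table 1 might be read as showing that controls are tested too. Section 2.8.4 is the more specific text and says otherwise, so the two need reconciling.

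**Conclusion.** The point stands for an exploratory analysis. Following Section 2.9.2 as written can yield a difference in deficiency that reflects testing and can then adjust for it. At an assumed equal prevalence of 30%, the chance of a spurious significant difference rises from 3.5% to 17% or 65% as the share of control deficiencies found falls from all to three quarters or half. Independently of ascertainment, choosing covariates by significance test lets in variables that arise after surgery and conception, and these can remove part of a total group difference. The gram figures rest wholly on assumed effects and show direction rather than expected size. The two GDM prevalences are not like for like, which limits that one outcome comparison. The primary analysis within the surgical group does not use the controls and is unaffected.

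**What to change.** 1. Take micronutrient deficiency out of the between-group tests and out of the between-group covariates. Keep it in the analyses within the surgical group. In controls, describe it together with the number tested.
2. Replace the rule that covariates enter when they differ with a prespecified set of pre-pregnancy covariates, for example parity, smoking and the matching factors, used whatever any test shows. Label any model that adds gestational weight gain or hypertension as a secondary analysis.
3. Report GDM by group descriptively, naming the test used in each. Compare hyperglycaemia between groups with the CGM metrics, which are obtained on the same schedule and with the same device in both.
4. Reconcile the micronutrient row of Table 1 with Section 2.8.4.

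The cost is wording only. Two exploratory comparisons, deficiency and GDM, become descriptive, and no new data are needed.

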## 2. Methods

### 2.1. Study Design and Setting

The GLORIA study is a prospective cohort study involving eight Belgian sites, investigating pregnancy outcomes following sleeve gastrectomy (SG) or RYGB. In a second stage, outcomes will be compared to a matched control group using an exploratory approach. SG has increasingly become the first-choice type of MBS for women of reproductive age. We estimate that between 30 and 50% of participants will have SG in the study. For each participant in the surgical cohort, an age- (≤2 years difference, and age > 40 will be rounded to 40 years) and BMI-matched (≤2 BMI points difference, matched to pre-pregnancy BMI) pregnant woman without history of MBS will be recruited. Seven Belgian hospitals were originally included to take part in the study: three university hospitals (UZ Leuven, UZ Antwerpen, and UZ Gent) and four large non-university hospitals (ZAS Palfijn, AZORG Aalst, Imelda Bonheiden, and AZ St-Jan Brugge). In 2023, one additional centre was added. All eight centres have previously participated in multicentre studies initiated by our research group [22,23]. Participating centres were selected for their expertise in endocrinology research, as well as obstetrical management of pregnant women with a history of MBS.

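### Fisher exact tests ignore the 1:1 matching that the outcome models respect, and on the natural reading they choose the covariates; the error is conservative and usually small

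*Protocol article*

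**What the plan says.** All of this is in the protocol article, section 2.9.2, Exploratory Comparative Analyses, unless another section is named.

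- **Design.** "The control group will be manually matched in a 1:1 ratio based on age and pre-pregnancy BMI before participation". Section 2.1 sets the limits: age within 2 years, and for each surgical participant a "BMI-matched (≤2 BMI points difference, matched to pre-pregnancy BMI) pregnant woman without history of MBS will be recruited". Section 2.8.1 lets a control join only when a one-to-one match exists.
- **Characteristics.** The comparison of the groups on parity, insufficient gestational weight gain, hypertension, deficiencies and smoking "will be performed using Fisher exact tests".
- **Outcomes.** Birth weight and glycaemic measures are compared with "linear mixed models with a random intercept to account for clustering by matching". Comparisons on binary outcomes "will be performed using a similar approach, applying generalised linear mixed models for binary responses".
- **Covariates.** "Confounders will be included as covariates in the model in case they were shown to differ between groups".
- **Test level.** The part of section 2.9.2 on the surgical group states that "all tests will be two-sided with significance set at" 0.05.

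**The concern.** One paragraph treats the same women in two ways. For outcomes, including binary ones, the two members of a pair are dependent. For binary characteristics they are independent. If pairs are alike on a characteristic, the unpaired test overstates the standard error of the group difference and rejects too rarely.

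This matters more than it would in a descriptive table because of the covariate rule. The Fisher comparison is the only comparison of these characteristics that the paragraph describes, so it is in effect the screen for confounders. A screen that errs towards no difference tends to leave an imbalanced characteristic out of the model. What is at stake is adjustment in the exploratory comparison of surgical women with controls.

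**Working it through.** **Inputs from the protocol article.** 1:1 matching on age and pre-pregnancy BMI (2.1, 2.9.2); two-sided 0.05 (2.9.2); n = 95 surgical women (2.9.1), taken here as 95 complete pairs. **Assumptions.** The prevalences and the within-pair correlation phi, neither of which the document gives.

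**Step 1: the plan's own figure.** No figure is stated for the Fisher tests; the 95 fixes the number of pairs. Reading the effect size 0.3 as a correlation, with test-wise alpha 0.025 and 80% power:

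- ((2.241 + 0.842) / atanh 0.3)² + 3 = 102.2
- add 4 covariates: 106.2
- times design effect 1 + 3 × 0.5 = 2.5, divided by 4 measurements: 66.4
- divided by 0.70 for missing measurements: 94.8, so 95

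The 95 reproduces. It was sized for the association within the surgical group, not for the matched comparison.

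**Step 2: direction.** With equal prevalence p in both groups, the variance of the difference in proportions across n pairs is 2p(1−p)(1−phi)/n. An unpaired test uses 2p(1−p)/n. The standardised difference therefore has standard deviation √(1−phi) instead of 1. Ignoring discreteness, a nominal 5% test has level 2 × [1 − Φ(1.96/√(1−phi))]:

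- phi 0.10: 1.96/0.949 = 2.066, level 3.9%
- phi 0.23: 1.96/0.877 = 2.234, level 2.5%

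Positive phi makes the test conservative. Discreteness lowers the level further.

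**Step 3: actual level.** Simulation of 95 pairs from a latent bivariate normal (20,000 sets), 20% in both groups. Fisher's level is about 3.3% at phi 0, 2.4% at phi 0.10 and 1.5% at phi 0.23. The first figure owes nothing to pairing: exact McNemar, which does use the pairs, is also at about 3% there.

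**Step 4: power for 35% versus 20%, same simulation.**

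| phi | Fisher | exact McNemar | mid-p McNemar |
|---|---|---|---|
| 0 | 58% | 57% | 63% |
| 0.05 | 58% | 60% | 65% |
| 0.11 | 59% | 63% | 68% |
| 0.23 | 59% | 69% | 74% |

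Fisher against exact McNemar isolates the cost of ignoring pairs: nothing at phi 0, about 1 to 4 points at 0.05 to 0.11, and about 9 to 10 at 0.23. The further 5 to 6 points to the mid-p column come from removing discreteness, since a similar gap is already there at phi 0.

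Other prevalences show the same pattern. For 30% versus 15%, Fisher against exact McNemar is 65 v 63% at a correlation of 0 and 68 v 79% at 0.3. For 30% versus 20% it is 30 v 29% and 27 v 39%.

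**Step 5: what phi is plausible.** Matching on age and BMI induces correlation in a characteristic only as far as it depends on age and BMI. An illustrative simulation of matching within the stated limits gave phi of about 0.02, 0.06, 0.15 and 0.28 for odds ratios of 1.3, 1.5, 2 and 3 per standard deviation of both factors. The larger losses in step 4 therefore need strong dependence on both.

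**The case against.** The case for leaving this alone has four parts.

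- **The effect is small.** At phi up to about 0.1 the cost is a few points of power, and no phi is given. This stands, and it limits the size of the point. A reader might take the gap to mid-p McNemar, up to 15 points (59 v 74%), as the price of ignoring pairs. It is not, because part of it is mid-p against exact.
- **The harm downstream is not shown.** A reader might infer that missed imbalances bias the group estimates of birth weight and glycaemia. That is possible in principle, but nothing in the document lets it be quantified. In the 35% versus 20% case Fisher's own power does not fall as phi rises; it only fails to gain. This stands.
- **The link to covariate choice is an inference.** The text does not name the Fisher p-value as the rule, and a fuller protocol may set out the procedure. The first part is right, but no other comparison of these characteristics is described, so it remains the natural reading.
- **McNemar would be a poor replacement.** It drops every pair with one member missing, and section 2.7 allows withdrawal and discontinuation. It also needs binary data, and it would keep selection by significance. This stands and shapes the fix.

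None of this removes the inconsistency. The unpaired test is a stated method, not a detail left for later, and the paragraph already names a model that would respect the pairs.

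**Conclusion.** The point holds as a minor inconsistency in a stated method. The Fisher tests ignore a dependence that the same paragraph models for outcomes, and they appear to act as the confounder screen. With positive within-pair correlation they are conservative, at about 2.4% at phi 0.10 and 1.5% at phi 0.23 for a nominal 5%. The loss of power that is due to pairing is slight unless a characteristic depends strongly on age and BMI.

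These sizes rest on 95 complete pairs, the assumed prevalences and the assumed phi. The documents do not support a reading that the tests inflate false positives: even at a correlation of −0.1 Fisher's level was at most about 4.4%. Nor do they support a reading that the main result is affected. The matched comparison is labelled exploratory, and the primary and secondary analyses use the surgical group only.

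**What to change.** Describe imbalance between the matched groups by standardised differences, and adjust the matched models for a confounder set fixed in advance instead of one selected by p-value. Candidates are the confounders that section 2.9.2 already lists (smoking, hypertension, nutrient deficiencies, insufficient gestational weight gain) plus parity, each only where measured comparably in both groups. Deficiencies need care: section 2.8.4 measures micronutrients every trimester in the surgical group, but in controls only on clinical judgement. Time from surgery, also listed, has no counterpart in controls. Whether weight gain and hypertension, which can arise during pregnancy, belong in the set should be settled on subject-matter grounds.

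If tests of characteristics are kept, use the generalised linear mixed model with a random intercept for the matched pair, as the paragraph already does for binary outcomes. It also keeps women whose match is missing.

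The cost is wording only, before analysis, with no change to data, visits or participants. The downside is a few more model parameters.
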